### 3.2. Evaluation of the Impact of SUPRANET

#### 3.2.1. Suicidal Ideation and Behaviour and Psychological Distress of the General Public

Suicidal ideation and behaviour of the general public will be measured in two ways: First, while challenging, because of the low base rate of completed suicide (11 per 100,000 in The Netherlands), suicide rates will be analysed using data from Statistics Netherlands. Trends in suicide rates during 2017–2019 in the seven SUPRANET communities will be compared to the national suicide trends. In 2015, the number of suicides in the SUPRANET communities was 166, on a population of 1,407,331 (11.8 per 100,000). Differences in suicide rates at baseline and after each implementation year will be calculated using incidence rate ratios. The hypothesis is that the multilevel intervention approach of SUPRANET will lead to a reduction in the suicide rate in the general population, as was found in other EAAD studies [6,7,8,9].

Secondly, the scores on the Suicidal Ideation Attribution Scale [15] in an online survey will be analysed. Four measurements will be carried out using on-line questionnaires among the general population. In each measurement, the national sample will be 1000 and the SUPRANET community sample will be 700 (in each SUPRANET community *n* = 100). The sample will be stratified by gender, age, education, region, and social class. The first measurement, the baseline, took place in January 2017. The second will take place just after the first wave of the public awareness campaign, the third in January 2018, and the fourth in January 2019. A fresh sample is taken for each of the four measurements to prevent learning effects and keep the comparison pure over time. Given an alpha of 0.05 and a power of 0.8, the sample will allow us to detect a small effect size of 0.08. The Suicidal Ideation Attribution Scale (SIDAS) consists of five items that are scored from 0 to 10 and assesses the frequency and controllability of suicidal thoughts, as well as the closeness to a suicide attempt, distress and interference with daily activities. We will investigate, using General Linear Model (GLM) repeated measures, if the changes measured in the SUPRANET communities are more improved than the changes measured nationally.

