#### 3.2.2. Public Attitudes, Stigma, and Taboo

The online survey among the general public partly replicates the baseline questionnaire for the general public of the Optimising Suicide Prevention Programmes and Their Implementation in Europe (OSPI-Europe) study [19], with Dutch translations of the Depression Stigma Scale [17] and the Attitude Towards Seeking Professional Psychological Help short form [18] (Table 1). We added questions about (talking about) suicidal behaviour, experience, taboo, and the Suicidal Ideation Attribution Scale (SIDAS) [15].

Changes in help-seeking behaviour, stigma, talking about suicide, and taboo around suicide will be analysed using GLM repeated measures. We will compare the results over time, as well as time × effect interactions to reveal if a SUPRANET community is differently (more) effective than the nationally-observed changes.

#### 3.2.3. Help-Seeking Behaviour to the Dutch Suicide Prevention Crisis Service 113

In addition to measuring an intervention effect within the general public with self-reporting, an intervention effect will also be measured by analysing the volume of crisis calls to the helpline of 113 Suicide Prevention. A significant increase in monthly calls during and just after the three waves of the public awareness campaign is hypothesized compared with the same months in the previous year [20]. Furthermore, due to the multicomponent approach, we expect bigger increases in crisis calls in the SUPRANET regions compared with the control region (i.e., national data outside the SUPRANET communities) [20]. This is feasible since the place of residence of each caller is monitored.

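### The online survey draws a fresh sample at each of four measurements but names a repeated-measures GLM, which needs the same respondents each time, so the analysis cannot validly be run as written

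*Protocol article*

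**What the plan says.** Section 3.2.1 of the protocol article sets out the survey: "Four measurements will be carried out using on-line questionnaires among the general population". At each one, "the national sample will be 1000 and the SUPRANET community sample will be 700", the latter made up of 100 from each of the seven communities. The sample is stratified by gender, age, education, region and social class. On who is measured, the section says: "A fresh sample is taken for each of the four measurements to prevent learning effects and keep the comparison pure over time".

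The same section gives the SIDAS analysis: "We will investigate, using General Linear Model (GLM) repeated measures, if the changes measured in the SUPRANET communities are more improved" than those seen nationally. Section 3.2.2 applies the method to the attitude outcomes: "Changes in help-seeking behaviour, stigma, talking about suicide, and taboo around suicide will be analysed using GLM repeated measures". It also states the comparison of interest: "We will compare the results over time, as well as time × effect interactions", to show whether change in a SUPRANET community differs from national change.

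Nowhere does the article describe a panel, a linkage of respondents between measurements, or a community-level unit that would be followed over time in both areas.

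**The concern.** A repeated-measures GLM separates variation between people from variation within people. It tests time and group × time against the within-person error, so each unit must be observed at every time point. Fresh samples rule that out by intention, because the aim is that nobody is asked twice. The sampling sentence and the analysis sentence in section 3.2.1 therefore cannot both stand.

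What is at stake is the controlled comparison of SUPRANET with national change on the survey outcomes named in sections 3.2.1 and 3.2.2. Section 3.1 counts suicidal ideation, and attitudes towards it, among the primary outcomes. An analyst who follows the text either has no complete rows to fit or must pair strangers by file order. The individual changes from such pairing mean nothing. Detail deferred to a fuller plan would not resolve this, since the article names the method twice and its own sampling excludes it.

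**Working it through.** **Inputs from section 3.2.1.** Four measurements; 1,000 national and 700 SUPRANET respondents at each; 7 communities × 100; alpha 0.05; power 0.8; stated detectable effect size 0.08. Sidedness, the effect-size metric and any intraclass correlation (ICC) are not given. Two-sided testing, outcomes in SD units and the ICC values below are assumptions.

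**1. The plan's own figure.** The 0.08 can be reproduced as Cohen's f with N = 1,000 + 700 = 1,700 and 3 numerator df. The noncentral F gives power 0.798 at f = 0.08 and a minimum detectable f of 0.0802. Both the metric and the N are inferred. A repeated-measures group × time calculation (1,700 people, four measurements) does not give 0.08: with assumed within-person correlations of 0 / 0.3 / 0.5 / 0.7, the detectable f is 0.040 / 0.034 / 0.028 / 0.022.

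**2. Can the named model be fitted?** Total respondents: 4 × 1,700 = 6,800. With one row per person and four time columns, each row has one filled cell. Complete rows: 0 of 6,800. There is no within-person error term.

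**3. Does a between-subjects model work on the same data?** An ordinary group × measurement model (3-df interaction, N = 6,800, independent respondents, no clustering) was simulated with no effect. Type I error was 0.0535 over 2,000 runs, against a nominal 0.05.

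**4. Precision of the contrast the plan wants.** For one follow-up against baseline, with independent samples:

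- SE = √[2 × (1/1000 + 1/700)] = √0.004857 = 0.0697 SD
- Minimum detectable difference in change = (1.960 + 0.842) × 0.0697 = 0.195 SD
- Power for a 0.08 SD difference in change = Φ(0.08/0.0697 − 1.960) = Φ(−0.81) ≈ 0.21

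For baseline against the mean of the three later measurements, SE = √[(4/3) × (1/1000 + 1/700)] = 0.0569 SD and the minimum detectable difference is 0.159 SD. Neither figure allows for clustering.

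**5. Community, under assumed ICCs.** Let the community-by-time ICC inflate the SUPRANET variance by 1 + 99 × ICC:

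- SE = √[2 × (1/1000 + (1 + 99 × ICC)/700)]
- Type I error if community is ignored = 2 × [1 − Φ(1.960 × 0.0697/SE)]

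| Assumed ICC | SE (SD) | Type I error if ignored |
|---|---|---|
| 0 | 0.0697 | 5.0% |
| 0.001 | 0.0717 | 5.7% |
| 0.002 | 0.0736 | 6.4% |
| 0.005 | 0.0792 | 8.5% |
| 0.01 | 0.0877 | 11.9% |
| 0.02 | 0.1025 | 18.3% |

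Simulation with 20,000 runs gave 8.3%, 12.3% and 18.2% at ICC 0.005, 0.01 and 0.02, in line with the formula.

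**The case against.** The strongest defence is that the phrase is used loosely for repeated cross-sections with time as a factor. The article does state the right comparison: change in SUPRANET communities against national change, tested as an interaction. On that reading the estimand, the samples and the data collection are sound, and only the model's name is wrong. Much of this stands, and it is why the repair is cheap. It does not remove the point. The name denotes a specific procedure, it is used in two sections, and nothing in the text signals the looser meaning.

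Four stronger readings are tempting, and the article does not support them.

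- **Falsely narrow intervals.** A reader might infer that the method would borrow a within-person correlation that does not exist and so understate the standard error. It would not. The fit estimates that correlation from the data, and for unrelated people it is about 0. In simulations that paired strangers by file order, without clustering, the mean SE was 0.0697 SD and type I error stayed at 5.3% to 5.5%.
- **Proven inflation from clustering.** A reader might infer that the test is anticonservative as it stands. That depends on an ICC the article does not give, and with a small ICC the effect is slight. All seven pilot communities are sampled with a fixed 100 each, so fixed community effects are also defensible if inference is confined to these seven.
- **A wrong power figure.** The 0.08 reproduces under one reading, so it is not an arithmetical error.
- **All outcomes affected.** The point does not reach suicide rates, K10, helpline calls or the general-practice outcomes. Nor does it reach the campaign-awareness questions in section 3.3.1, which sit in the same survey without this method.

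**Conclusion.** The mismatch is real and rests on the article's text alone: independent samples by design, and a named method that needs linked respondents. As written, the analysis of SIDAS, stigma, help-seeking, talking about suicide and taboo cannot validly be carried out. The main consequence is an unusable specification; a demonstrated bias or a misleadingly small standard error is not part of it.

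Once the model is corrected, the difference in change between baseline and one follow-up has an SE of about 0.070 SD and a minimum detectable value of about 0.195 SD. This assumes equal variances, two-sided 5%, 80% power and no clustering. The stated 0.08 does not describe this contrast in SD units, so the detectable effect needs restating.

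The community issue is secondary and conditional. Assumed community-by-time ICCs of 0.001 to 0.02 would give a type I error of about 6% to 18% if community were ignored.

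**What to change.** In sections 3.2.1 and 3.2.2, replace the repeated-measures GLM with a regression on all independent respondents:

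- Area (SUPRANET or national), measurement and area × measurement as between-subject terms. The effect is the area × measurement contrast, with the follow-up or follow-ups that define it stated.
- Adjustment for the sampling strata: gender, age, education, social class, and region where it is not collinear with area.
- The fresh samples kept as they are.
- The detectable effect restated for this contrast, with metric and sidedness given.
- A community × measurement variance component within the SUPRANET arm with small-sample degrees of freedom, at least as a sensitivity analysis. Cluster-robust standard errors across both areas are poorly defined here, because the national 1,000 is not divided into comparable clusters.

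The cost is a change of analysis wording and a recalculated detectable effect. No new data are needed, and intervals may be wider if community variation is present.

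### GLM repeated measures is named for SIDAS and the attitude outcomes, but each survey measurement draws new respondents, so the respondent-level test does not fit the sampling design

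*Protocol article*

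**What the plan says.** Section 3.2.1 of the protocol article sets out the survey: "Four measurements will be carried out using on-line questionnaires among the general population". On size it states: "In each measurement, the national sample will be 1000 and the SUPRANET community sample will be 700", the latter being 100 from each of seven communities. The sample is stratified by gender, age, education, region and social class. On who is sampled: "A fresh sample is taken for each of the four measurements to prevent learning effects and keep the comparison pure over time".

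The same section gives the analysis of SIDAS: "We will investigate, using General Linear Model (GLM) repeated measures, if the changes measured in the SUPRANET communities are more improved" than those seen nationally. Section 3.2.2 names the same method for the other attitude measures: "Changes in help-seeking behaviour, stigma, talking about suicide, and taboo around suicide will be analysed using GLM repeated measures". It adds "time × effect interactions to reveal if a SUPRANET community is differently (more) effective than the nationally-observed changes".

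Section 3.2.1 also states that, at alpha 0.05 and power 0.8, an effect size of 0.08 can be detected. It does not name the metric, the sidedness or the test.

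The article describes no panel, no identifier linking respondents across measurements, and no aggregated unit to be followed over time.

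**The concern.** GLM repeated measures takes the values of each subject at every time point and tests time and time-by-group against the residual variation within subjects. A respondent who is surveyed once contributes nothing to that residual. With the respondent as subject, the sampling scheme rules out the named test. This is not a detail left to a fuller document: the article states the method, and its own design excludes it.

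Section 3.1 places the primary outcomes on suicidal ideation and behaviour and attitudes toward them. GLM repeated measures is the only stated analysis for SIDAS and for the attitude measures, so it carries question 1(b) and the SIDAS part of question 1(a). An analyst following the text would either have no complete case or would have to place unrelated people on one row. A reader could also expect the precision of a followed cohort, which fresh samples do not give.

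**Working it through.** **Inputs from section 3.2.1.** Four measurements; 1000 national and 700 SUPRANET (7 × 100) respondents at each; new respondents each time; alpha 0.05; power 0.80; stated detectable effect 0.08.

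**1. The stated 0.08.** Of the variants tried, one reproduces it: Cohen's f from an independent-groups F test with 3 numerator degrees of freedom and N = 1700. The required noncentrality is 10.93, so f = sqrt(10.93/1700) = 0.0802, and power at f = 0.08 is 0.798. This variant uses no within-person correlation. The match does not show that this test was the one used. The point made here does not depend on the figure.

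**2. Observations per respondent.** 4 × (1000 + 700) = 6,800 responses. In a mock data set built to this design, each person has one value. Reshaped to one row per person, it has 0 complete cases, so there is no within-respondent error term.

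**3. What can be fitted.** A between-respondents linear model with group, measurement and group × measurement has 2 × 4 = 8 parameters and 6,800 − 8 = 6,792 residual degrees of freedom. The contrast that sections 3.2.1 and 3.2.2 ask for is the interaction in this model.

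**4. Precision with fresh samples, two waves, no clustering.**
- SE of the difference in change = sqrt(2/700 + 2/1000) = sqrt(0.004857) = 0.0697 SD.
- Detectable difference = (1.960 + 0.842) × 0.0697 = 0.195 SD.
- If 0.08 were read as a difference in change in SD units, power would be Φ(0.08/0.0697 − 1.960) = Φ(−0.81), about 21%.
- Baseline against the mean of the three later waves: 2.802 × sqrt((1/700 + 1/1000) × (1 + 1/3)) = 0.159 SD.

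**5. A followed cohort, for comparison.** The SE in step 4 would be multiplied by sqrt(1 − ρ). The article gives no ρ, so the values are assumptions.

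| Assumed ρ | SE (SD) | Detectable (SD) |
|---|---|---|
| 0 (fresh samples) | 0.070 | 0.195 |
| 0.3 | 0.058 | 0.163 |
| 0.5 | 0.049 | 0.138 |
| 0.7 | 0.038 | 0.107 |

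**6. Sensitivity to clustering.** Suppose respondents in the same community and wave share a correlation ICC (assumed; none is given) and the national sample is not clustered. The SUPRANET term is then inflated by 1 + 99 × ICC.
- ICC 0.001: factor 1.099; SE = sqrt(2 × 1.099/700 + 2/1000) = 0.072; detectable 0.201 SD.
- ICC 0.01: factor 1.99; SE = sqrt(2 × 1.99/700 + 2/1000) = 0.088; detectable 0.246 SD.

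**The case against.** The best defence is that the label is loose wording for a time-by-group model. The target contrast is clear from both sections and the design supports it. Much of this stands: the question, the data and the group-by-wave means survive, and only the named test is wrong. But GLM repeated measures is a specific procedure and it is named twice, so the text has to be changed if something else was meant.

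A second defence is that community means, or means of stratification cells, could be the repeated unit, since the same seven communities are sampled each time. That is possible in principle. The article does not plan it, and it describes the national comparator as a single sample. Likewise a person could be drawn twice by chance, but the design neither intends nor links this.

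Four stronger readings are tempting, and the document does not support them.
- *Nothing can be estimated.* Step 3 shows otherwise.
- *False-positive rates would be badly inflated.* If unrelated rows were forced together, the point estimates would not change. In a simulation with 1,700 rows and four independent columns, random row order gave a type I error of 5.3%. Gross inflation appeared only when each wave was sorted by score, which nothing in the article suggests.
- *The sample size relied on within-person correlation.* No such correlation is stated, and step 1 reproduces 0.08 without one.
- *Every survey outcome is affected.* The campaign awareness and recognition questions in section 3.3.1 are not assigned this method.

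**Conclusion.** Wrong as written. The sampling scheme in section 3.2.1 and the method named in sections 3.2.1 and 3.2.2 cannot both stand at respondent level. The outcomes affected are SIDAS, help-seeking, stigma, talking about suicide and taboo. Suicide rates (incidence rate ratios), the K10 from the Health Monitor and helpline calls are not affected.

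The detectable two-wave difference in change is about 0.195 SD. This assumes independent respondents, equal SD in all groups and waves, full planned numbers, two-sided alpha 0.05 and 80% power. It is larger if community clustering matters. The conclusion that test and design do not match needs none of these assumptions; it follows from the text alone.

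**What to change.** In sections 3.2.1 and 3.2.2, replace GLM repeated measures by a between-respondents regression for independent cross-sections, with group (SUPRANET or national), measurement (categorical) and group × measurement. Define the effect as the interaction contrast against January 2017. Do not declare respondent as a within-subject factor.

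Adjust for the stratification variables and account for sampling within seven communities, for example by community terms and community-specific changes. A model that treats all 6,800 respondents as independent could give intervals that are too narrow. Restate the detectable effect for the interaction, with its metric and sidedness.

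The cost is two sentences of analysis wording, the restated detectable effect, slightly more analysis work, and possibly wider intervals once clustering is allowed for. No new data are needed.

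### The survey's detectable effect of 0.08 has no stated scale and does not match the planned difference in change, whether read in SD units or as Cohen's f

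*Protocol article*

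**What the plan says.** Section 3.2.1 of the protocol article sets the size of each survey round: "In each measurement, the national sample will be 1000 and the SUPRANET community sample will be 700", with 100 respondents in each of the seven communities. There are four rounds, and respondents are not followed up: "A fresh sample is taken for each of the four measurements to prevent learning effects and keep the comparison pure over time". The analysis, described as a repeated-measures general linear model, asks whether SIDAS scores improve more in the SUPRANET communities than nationally. Section 3.2.2 applies the same model, with an interaction with time, to the stigma, taboo and help-seeking outcomes from the same survey.

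The power statement is a single sentence: "Given an alpha of 0.05 and a power of 0.8, the sample will allow us to detect a small effect size of 0.08". It does not say whether 0.08 is a difference in SD units, Cohen's f or something else. It also does not say which test, how many measurements or how many sides it refers to.

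**The concern.** The estimand is a difference between two changes, and each change is estimated from separate samples of people. Such a contrast has twice the variance of a single cross-sectional comparison, with no within-person correlation to recover precision. A detectable effect of 0.08 looks very small for 700 against 1,000, and a reader who meets an unlabelled effect size for a mean score may well take it as SD units.

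Section 3.1 makes suicidal ideation and behaviour, and attitudes towards them, the primary outcomes. Section 3.2.1 itself calls the suicide-rate comparison challenging because suicide is rare, so the survey carries much of the evidence. If 0.08 is taken as SD units, a null SIDAS or stigma result could be read as evidence against effects that the survey would usually miss. If it is Cohen's f, the sentence describes a calculation that does not fit four fresh samples, and readers cannot tell how large an effect is meant.

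**Working it through.** **Inputs from section 3.2.1.** Alpha 0.05, power 0.80, 700 SUPRANET and 1,000 national respondents per measurement, four measurements, new respondents each time. Total 4 × 1,700 = 6,800 independent responses.

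**Assumptions.** Two-sided test (sidedness is not stated); outcome scaled to SD = 1; no clustering until the last step.

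**Reproducing 0.08.** Two calculations arrive at it.
- Cohen's f, 3-df F test, non-centrality λ = f²N. With N = 1,700 and f = 0.08, λ = 0.0064 × 1,700 = 10.88 and power is 79.8%. The f detectable at 80% is 0.0802, and f = 0.08 needs N = 1,708.
- A group difference after pooling the three later measurements (2,100 against 3,000) and ignoring baseline: 2.802 × √(1/2,100 + 1/3,000) = 0.080 SD, with 80.3% power at 0.08 SD.

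Neither is the planned contrast. The first spreads one measurement's sample over a test that needs all four measurements. The second drops the baseline, so it does not measure change.

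**SD units, planned contrast.** Detectable effect = (1.960 + 0.842) × SE. Power at 0.08 SD = Φ(0.08/SE − 1.960). The one-measurement standard error is √(1/700 + 1/1,000) = 0.0493.

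| Contrast | SE | Detectable effect | Power at 0.08 SD |
|---|---|---|---|
| One measurement, SUPRANET v national | 0.0493 | 0.138 SD | 36.8% |
| Difference in change, two measurements | 0.0493 × √2 = 0.0697 | 0.195 SD | 20.8% |
| Difference in change, baseline v mean of three later | 0.0493 × √(4/3) = 0.0569 | 0.159 SD | 29.0% |

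One-sided testing does not bring these to 0.08: the two-measurement figure becomes 0.173 SD (31% power at 0.08 SD). The last row assumes the same effect at all three later measurements. A 3-df group-by-time test on all 6,800 responses, under that same constant effect, detects 0.188 SD (19% power at 0.08 SD).

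**Cohen's f, planned contrast.**
- All 6,800 responses, 3-df interaction: detectable f = 0.040. At f = 0.08, λ = 0.0064 × 6,800 = 43.52 and power exceeds 99.9%.
- Two measurements, 3,400 responses, 1 df: detectable f = 0.048. At f = 0.08, λ = 21.76 and power is 99.7%.
- f = 0.08 translated to a two-measurement difference in change: 0.08 × √3,400 × 0.0697 = 0.325, about 0.33 SD.

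**Clustering (assumed).** The documents give no intraclass correlation. With 100 respondents per community, the design effect on the SUPRANET sample is 1 + 99 × ICC. The two-measurement detectable effect is 2.802 × √(2 × (DE/700 + 1/1,000)).

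| Assumed community-by-time ICC | DE | Detectable difference in change |
|---|---|---|
| 0.005 | 1.495 | 0.222 SD |
| 0.01 | 1.99 | 0.246 SD |
| 0.02 | 2.98 | 0.287 SD |

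**The case against.** The strongest reply is that the SD scale is the reader's assumption. The article speaks only of an effect size, and Cohen's f suits a general linear model over four measurements. Section 3.3.4 also calls 0.10 a small effect size, which fits the usual labelling of f better than that of a standardised mean difference. On the f reading 0.08 reproduces almost exactly, and using the true 6,800 responses makes the printed claim conservative. Since f = 0.08 is about 0.33 SD in a two-measurement change, it even lies above the 0.22 to 0.29 SD range obtained with the assumed clustering.

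Much of this stands. A reader might infer that the survey cannot deliver its stated effect and has only 21% power. The document does not support that without a condition: the 21% applies only if 0.08 means SD units and the contrast is between two measurements. A reader might also take "to reveal if a SUPRANET community is differently (more) effective than the nationally-observed changes" as a plan to test each community of 100 separately. The phrase may be generic, and section 3.2.1 asks about the communities together, so nothing here rests on single-community power.

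What does not stand is that the f reading rescues the sentence. Its N of 1,700 is incompatible with four fresh samples, and on the correct N the detectable f is half the printed value. Nor is this detail that a condensed article leaves elsewhere: the article prints the figure, and the figure does not fit the design printed beside it.

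**Conclusion.** The point holds in a conditional form. The 0.08 has no stated scale and is not the detectable effect for the planned difference in change on either plausible scale. In SD units it is too small by a factor of about two to two and a half (0.159/0.08 = 2.0; 0.195/0.08 = 2.4). As Cohen's f it is too large by a factor of two (0.080 against 0.040), and it then describes an effect of about 0.33 SD.

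This rests on a two-sided 0.05 test, independent samples at each measurement, equal variances and no clustering. The clustered range of 0.22 to 0.29 SD is illustrative only. The defect is in the stated figure. It does not show that the sample is inadequate, because the article names no effect in SD units that the survey must detect.

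**What to change.** Replace the power sentence in section 3.2.1 with one that names the scale and the contrast, for example:

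*With 700 and 1,000 independent respondents per measurement, the study has 80% power (two-sided 0.05) to detect a SUPRANET–national difference in change of about 0.20 SD between two measurements (about 0.16 SD for baseline versus the mean of the three later measurements), before allowing for clustering in the seven communities.*

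If a clustered figure is added, label it as an assumption: 0.22 to 0.29 SD for two measurements at an ICC of 0.005 to 0.02. If Cohen's f was intended, say so, base it on the independent responses that the test will use, and give the SD equivalent.

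The cost is one sentence, with no change to sample size or design. The restated figure is less favourable than the printed one if 0.08 was meant in SD units, and more favourable if it was meant as f.
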